Most therapeutic drug monitoring studies of cloxacillin involve critically ill patients with SAB in the intensive care unit (ICU) or patients with infective endocarditis.^14^,^16^ However, the typical patient with SAB is older (66–75 years) without endocarditis and is treated outside of the ICU.^17^,^20^ In younger patients outside the ICU, a small study in which total concentrations were measured suggests a low probability of achieving 100% fT>MIC with intermittent cloxacillin dosing regimens.^21^ However, these results may not be applicable to an elderly population, among whom an increased prevalence of chronic kidney disease can be anticipated,^22^ since augmented renal clearance is a risk factor for insufficient exposure of beta-lactam antibiotics.^23^ Estimation of renal function has shown potential in identifying insufficient exposure among ICU patients for some low-to-medium protein bound beta-lactam antibiotics,^24^ but the relevance for highly protein bound antibiotics among patients with SAB outside of the ICU is unknown.

Acute kidney injury (AKI) is common for patients with SAB, with a reported incidence between 17% and 43%, and is associated with an increased 30-day mortality.^25^,^27^ Although AKI has been considered to be caused by the infection per se, treatment with isoxazolyl penicillins has also been associated with an increased risk of nephrotoxicity.^28^ There are limited data on whether the increased risk of isoxazolyl penicillin-induced AKI is concentration-dependent, but small studies suggest that about 57%–71% of patients with manifest AKI had a cloxacillin concentration above 50 mg/L.^29 30^ The reported median time of AKI recovery after cloxacillin cessation is 5 days, which implies that early detection of AKI is beneficial for timely dose adjustment.^29^ However, an increase of serum creatinine as a routine marker for kidney injury is rarely detected until 1–2 days after AKI onset. AKI onset usually occurs within days after therapy initiation,^29^ suggesting the development of acute tubular necrosis.^29 31^ Biomarkers of renal tubular injury may have the potential to detect AKI at an earlier stage than serum creatinine,^32^ but their diagnostic potential has not been widely evaluated in patients treated with beta-lactam antibiotics.^33^

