### Trial population

The trial population will consist of adult patients with a blood culture with growth of *Staphylococcus aureus,* obtained no more than 72 hours prior to inclusion. The participant is treated with cloxacillin therapy started at the time of, or no more than 72 hours prior to, inclusion, and has given informed consent. Inclusion and exclusion criteria are found in table 1. Patients will be treated with standard-of-care according to the treating physician, normally intravenous cloxacillin 2 g every 6–8 hours for at least 7 days.

**Table 1 T1:** Inclusion and exclusion criteria

Inclusion criteria	Exclusion criteria
Positive blood culture with *Staphylococcus aureus* obtained no more than 72 hours before inclusion	*S. aureus* not susceptible (S) to cloxacillin
≥18 years of age	Polymicrobial bacteraemia or concomitant infection which demands treatment with an antibiotic with broader spectrum than cloxacillin.
Treatment with cloxacillin, started at inclusion or no more than 72 hours before inclusion	Endocarditis or other intracardial infections detected by echocardiography.
Informed oral and written consent	Serious allergic reaction to cloxacillin, other penicillins or cephalosporins.
	Any contraindication for cloxacillin treatment or trial participation as judged by the treating physician.
	Moribund; when a cure is not deemed achievable with active treatment and aim of care is to give end-of-life or best supportive care
	Breastfeeding and not able or willing to interrupt breastfeeding
	Unconsciousness, not willing to participate or assessed as having difficulties understanding the significance of trial participation due to mental disability or language barriers.
	Participation in a clinical trial 30 days prior to initiation
	Prior participation in the current trial

Cloxacillin susceptibility is assessed using clinical break-points from 2025 by the European Committee on Antimicrobial Susceptibility Testing (EUCAST).^5^

Participants with no available echocardiography at the time of inclusion may still be recruited. If endocarditis is detected with echocardiography later during the trial, the participant will be excluded.

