### Trial procedures

The trial duration for each participant will be 30 days. Initial blood and urine sampling will occur during the first 7 in-hospital days, and outcome data will be gathered on day 30 from the medical record (table 2).

Each positive blood culture will be reported to an infection specialist by direct contact from the microbiology lab at each site. Eligibility of trial participation will be assessed, where eligible patients are informed about and asked to participate in the trial by a doctor or nurse associated with the trial. After written informed consent is obtained, participant characteristics are registered (gender, age, weight, height). Comorbidity will be estimated using the Charlson comorbidity index.^37^ Infection severity will be estimated via the National Early Warning Score 2.^38^ Current medications and dosing at time of inclusion will be recorded as will any addition, withdrawal or dosing adjustments during the trial duration. Prevalence of neurologic symptoms will be registered with occurrence of tremor, hallucination, convulsions or confusion corresponding to ≥2 points measured by Nursing Delirium Screening Scale,^39^ as well as consciousness level assessed using the Reaction Level Scale-85.^40^ Blood cloxacillin concentrations will be sampled prior to administration (trough) as well as within 30 min after end of cloxacillin infusion (peak) (table 2). Additional measurements of plasma liver and renal biomarkers (alanine aminotransferase (ALT), cystatin C, creatinine and albumin) and blood cultures (aerobic+anaerobic) will be sampled at the same time as clinical sampling or trough level sampling.

**Table 2 T2:** Trial procedures

Procedures	Day							
	1	2	3	4	5	6	7	30 (28–35)
Inclusion/exclusion criteria eligibility	√							
Informed consent	√							
Demographic and clinical data, comorbidity, current medication, baseline symptoms CNS	√							
Neurological symptoms, NEWS-2, medication and dosing adjustments	√	√	√	√	√	√	√	
Plasma samples: ALT, cystatin C, albumin.	√					√		
Plasma creatinine, eGFR estimation	√	√	√	√	√	√	√	
Urine sample for renal damage marker measurement and initiation of 12 hours urine sampling for creatinine clearance measurement	√					√		
Plasma samples for cloxacillin-concentration measurement (peak and trough) and urine creatinine measurement with creatinine clearance calculation		√					√	
Blood culture		√	√	√			√	
Final diagnosis, duration of bacteraemia, mortality, complexity of infection								√

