### Selected cloxacillin PK/PD targets for efficacy and toxicity

Methicillin-susceptible *S. aureus* shows a cloxacillin MIC distribution epidemiological cut-off (ECOFF) breakpoint at 0.5 mg/L, based on wild-type distributions from the EUCAST.^42^ Thus, the exposure target in this trial is set to 100% fT>MIC_ECOFF_, maintaining an unbound concentration above 0.5 mg/L.^11^ Overexposure is defined as maintaining an unbound concentration above 5 mg/L (100% fT>10xMIC_ECOFF_) or a corresponding total concentration above 50 mg/L, which was found in >50% of patients with a manifest AKI.^29 30 43^ AKI will be assessed by the change of serum creatinine levels, as described in Kidney Disease: Improving Global Outcomes (KDIGO) criteria.^44^ Neurological symptoms such as persistent coma and delirium have been associated with increased total trough cloxacillin concentrations with a lower range of 100 mg/L.^16^

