### Endpoints

Primary endpoints:

Proportion of patients with SAB reaching 100% ƒT>MIC_ECOFF_, that is, an unbound cloxacillin trough level of >0.5 mg/L at days 2 and 7 and its association with renal function.Proportion of patients with SAB reaching an unbound cloxacillin trough level of >5 mg/L or total trough level of >50 mg/L at days 2 and 7 and its association with renal function.

Secondary endpoints:

Prevalence of increased levels of urine markers for renal tubular damage (cystatin C, KIM-1, NAG, NGAL, A1M) compared with reference values, and its association with cloxacillin concentrations (peak and trough) at days 2 and 7.Prevalence of AKI based on creatinine, defined by KDIGO, measured daily between days 1 and 7.Onset of new symptoms from the central nervous system (ie, decreased consciousness, seizures, tremor, hallucinations or confusion), with day 1 regarded as baseline, measured daily on days 1–7, in relation to cloxacillin concentrations (peak and trough) at days 2 and 7.Descriptive characteristics of the SAB population, including sex, age, weight, comorbidity, medications, infection severity, complexity, duration and 30-day mortality.Levels of additional exploratory biomarkers in urine and plasma associated with nephrotoxicity or neurotoxicity.The trial participants’ experience taking part in the trial.

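### New CNS symptoms are counted from a day-1 baseline that can fall up to 72 hours after the first cloxacillin dose

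*Protocol article*

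**What the plan says.** The secondary CNS endpoint in Endpoints covers only symptoms that are new, "with day 1 regarded as baseline, measured daily on days 1–7", and relates them to peak and trough cloxacillin concentrations on days 2 and 7. Table 2 (Trial procedures) puts eligibility and consent on day 1 and collects on that day "Demographic and clinical data, comorbidity, current medication, baseline symptoms CNS".

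Treatment may begin earlier than that. Table 1 (Trial population) requires "Treatment with cloxacillin, started at inclusion or no more than 72 hours before inclusion".

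The kidney endpoints are worded differently. The AKI endpoint is "Prevalence of AKI based on creatinine, defined by KDIGO, measured daily between days 1 and 7". The section on PK/PD targets adds that "AKI will be assessed by the change of serum creatinine levels", following KDIGO. Neither place names the reference creatinine. Urinary tubular markers are compared with reference values (Sample analysis; Endpoints), not with day 1.

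Statistical analysis describes the secondary results as exploratory.

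**The concern.** An endpoint defined as new onset depends on where its baseline sits relative to exposure. Here the baseline is tied to inclusion, not to the first dose. For a patient included late, the baseline is an on-treatment assessment. Confusion or tremor that appeared after the first dose and is still present on day 1 is then recorded as a pre-existing state.

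The time axis is also mixed. Days 1 to 7 are trial days, so the same label means different lengths of exposure in different patients. In the analysis relating CNS symptoms to concentration, one patient is observed over the first week of therapy and another from about the fourth day onward. If nothing records the difference, a weak or absent association would be hard to interpret.

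**Working it through.** **Inputs.** Start of cloxacillin 0 to 72 hours before inclusion (Table 1); inclusion on day 1 (Table 2); usual dosing interval 6 to 8 hours (Trial population), used only to count doses; concentrations on days 2 and 7 (Table 2).

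**Doses before baseline.** Delay divided by interval, at the longest delay: 72/8 = 9 and 72/6 = 12 doses.

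**Trial day against treatment day.** Approximate treatment day = trial day + delay in hours/24.

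| Delay (h) | Trial day 1 | Trial day 2 | Trial day 7 |
|---|---|---|---|
| 0 | 1 | 2 | 7 |
| 24 | 2 | 3 | 8 |
| 48 | 3 | 4 | 9 |
| 72 | 4 | 5 | 10 |

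The day-2 sample thus falls on about treatment day 2 to 5, and the CNS window runs from treatment days 1–7 to about days 4–10.

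**How a symptom is classified.** Take a symptom absent before the first dose that starts 30 hours later, in a patient included at 72 hours. If it persists on day 1, it is baseline and not an event. In a patient included at the first dose, the same symptom at the same time is a new event.

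**Size, as illustration only.** The documents give no distribution of delay and no onset timing for CNS symptoms. Assume exponential onset with a median of 48 to 120 hours from first dose. The share of onsets before day 1 is then 1 − 0.5^(delay/median):

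- 24 h delay: 13% to 29%
- 48 h delay: 24% to 50%
- 72 h delay: 34% to 65%
- no delay: 0%

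These follow entirely from the assumed medians. They also include symptoms that resolve before day 1, which would not be recorded as baseline. They are not an estimate for this trial.

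**AKI, conditional.** Background states that "AKI onset usually occurs within days after therapy initiation", and day 1 is the first creatinine that Table 2 schedules. Suppose day 1 were the reference. A true rise to 1.6 times the pre-treatment value, with 1.4 times already reached on day 1, would read as 1.6/1.4 = 1.14. If a pre-treatment clinical value is the reference, nothing is lost. The article does not say which applies.

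**Sample size.** The plan's figure is 38 + 57 = 95. For overexposure of 50% against 20%, ratio 57/38 = 1.5, two-sided alpha 0.05 and power 0.80, the normal-approximation formula for two proportions with continuity correction gives 37 + 56 = 93, within two patients. No toxicity event enters this calculation, so the present point does not touch it.

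**The case against.** The day-1 baseline has good reasons behind it. Consent is obtained that day, so it is the first time the trial can apply its structured delirium and consciousness scales. Symptoms present then are recorded, not lost. Concentrations are first measured on day 2, so counting events from the first dose would place some outcomes before the exposure they are related to. It would also add early events driven by the infection. Chart notes on confusion are not comparable with prospective scales. All of this stands, and it is why day 1 should remain the main definition. It does not answer the uneven treatment windows or the classification of on-treatment symptoms as baseline.

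A reader might infer four stronger things that the documents do not support:

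- **Early kidney injury is absorbed into baseline.** The day-1 rule is stated for CNS symptoms only. AKI is a KDIGO prevalence, and a condensed article may leave its reference creatinine to the full protocol. Background also notes that "an increase of serum creatinine as a routine marker for kidney injury is rarely detected until 1–2 days after AKI onset", so injury that began shortly before inclusion may still show as a rise within days 1 to 7.
- **Tubular damage is absorbed.** These markers are judged against reference values, so damage present on day 1 is counted.
- **The bias runs toward no effect.** It would if the symptoms classed as baseline were concentration-related. If they were mainly caused by the infection, setting them aside could sharpen the association.
- **A definite share of events is lost.** Any percentage rests on assumed delays and onset times.

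**Conclusion.** The point holds for the CNS endpoint. On the plan's own text, a symptom that begins on treatment before day 1 and persists cannot count as new, and trial days correspond to treatment days that differ by up to three between patients. Patients who start cloxacillin at inclusion are unaffected. How many are affected, and in which direction the association moves, cannot be derived from the documents.

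For AKI the point applies only if day 1 is in fact the reference creatinine. It does not extend to the tubular markers' comparison with reference values. The endpoints concerned are secondary and exploratory, and the primary endpoints and N = 95 are unchanged. This is a cheap improvement, not a flaw that threatens the trial's main conclusions.

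**What to change.** Keep the prospective day-1 assessment as the main definition of CNS baseline, and add:

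1. Record hours from first cloxacillin dose to day 1 and, where the medical record allows, CNS status before the first dose.
2. Include time since first dose in the analysis of CNS symptoms against concentration.
3. Add two sensitivity analyses: (a) count symptoms present on day 1 but absent before the first dose as treatment-period events; (b) restrict to patients included within 24 hours of the first dose.
4. If day 1 would otherwise serve as the KDIGO reference creatinine, use the last available clinical value before treatment, with day 1 as fallback.

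The cost is a few retrospective fields and a short addition to the analysis plan. The start of cloxacillin must already be known to check eligibility, medical-record data already go into the eCRF, and recruitment is planned to run to a preliminary date of 31 December 2026. The downside is that pre-dose chart data are less standardised than the trial scales and will be missing for some patients. Analysis (a) should therefore be labelled supportive, and the number of patients without pre-dose information reported.

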## Introduction

### Background

*Staphylococcus aureus* bacteraemia (SAB) is a severe infection with a reported prevalence of 9.3–65 cases/100 000/year and a 30-day and 90-day mortality rate ranging from 14%–23% and 24%–32%, respectively.^1^,^3^ Isoxazolyl penicillins, such as cloxacillin, are considered a first-line therapy when treating methicillin-susceptible SAB.^4^ Standard dosage of intravenous cloxacillin for SAB varies depending on infection severity and local dosing recommendations.^5 6^ Currently, a dose of 2 g every 6–8 hours is recommended for SAB without endocarditis in Sweden.^7 8^

In general, beta-lactam antibiotics show a time-dependent efficacy, where an insufficient percentage of the dosing interval during which the unbound (free) antibiotic concentration remains above the minimum inhibitory concentration (MIC) (fT>MIC) increases the risk of clinical failure and resistance development.^9 10^ For severe infections, it is recommended that unbound (free) plasma concentration remains above the MIC of the pathogen during therapy (100% fT>MIC).^11^ Cloxacillin is highly protein bound, like other isoxazolyl penicillins (eg, dicloxacillin and flucloxacillin), with an unbound fraction of 6%–8% based on data from the manufacturer.^7 12^ There are limited data on whether recommended dosing of intermittently given cloxacillin is sufficient to reach the recommended target in real-world patients with SAB. Since flucloxacillin protein binding has shown a variability between 2% and 72% in critically ill patients,^13^ an individualisation of cloxacillin dosing may be warranted.

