Serious adverse events (deaths)		√	√	√	√	√	√	√
End of trial								*√*

ALT, alanine aminotransferase; CNS, central nervous system; eGFR, estimated glomerular filtration rate; NEWS, National Early Warning Score.

Urine will be sampled for renal tubular damage biomarker measurements (cystatin C, kidney injury molecule 1 (KIM-1), N-acetyl-β-D-glucosaminidase (NAG), neutrophil gelatinase associated lipocalin (NGAL), alpha-1-microglobulin (A1M) and additional biomarkers associated with renal damage). A 12-hour urine collection will subsequently be initiated to measure creatinine clearance and total urine production (table 2). Total urine volume will be determined by weight and sampled for creatinine clearance analysis.

At the end of the trial participation, mortality, lost-to-follow-up, time to negative SAB blood culture, assessment of SAB complexity according to Infectious Diseases Society of America,^41^ and diagnosis codes will be collected from the medical record.

More details on the frequency of data and sample collection can be found in table 2.

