### Sample analysis

Plasma ALT, cystatin C, creatinine and albumin as well as urine A1M and urine creatinine clearance will be analysed using validated clinical routine methods at accredited hospital laboratories. Cloxacillin samples will be centrifuged (2000 g, 10 min) within 1 hour of sampling, aliquoted into 6×500 µL cryotubes and stored in −80°C until analysis. Total and free fraction of cloxacillin will be analysed at Karolinska University Laboratory (Stockholm, Sweden), using ultrafiltration and LC-MS/MS with validated methods available in clinical routine.^45^

Renal tubular damage biomarkers will be analysed from frozen urine at Academic Laboratory (Uppsala, Sweden), where KIM-1 and NGAL will be analysed using commercial sandwich ELISAs (R&D Systems, Bio-Techne, Dublin, Ireland), and urine cystatin C and NAG with a Mindray BS380 chemistry analyser (Mindray Medical International, Shenzhen, China). The reference intervals used will be <0.414 mg/L (cystatin C^46^) and <10 mg/L (A1M). As there is no internationally recognised reference material for KIM-1, NAG and NGAL, the standard interval will be set to two SD above the mean for each assay according to the manufacturer. Additional urine renal damage biomarkers may come to be analysed using validated methods.

On day 30 (28–35), a proportion of the trial subjects will be asked about their experience of the trial through a questionnaire or a brief, semistructured interview to provide feedback on their experience of participation in the trial.

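### Table 2 allows 30-day mortality to be read, and the patient closed, from day 28, so deaths on days 29–30 can be missed

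*Protocol article*

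**What the plan says.** The secondary endpoints (protocol article, Endpoints) include descriptive characteristics of the population, ending with "infection severity, complexity, duration and 30-day mortality".

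The running text under Trial procedures fixes the time point at day 30: "The trial duration for each participant will be 30 days", and "outcome data will be gathered on day 30 from the medical record". That second sentence points the reader to Table 2.

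Table 2 is looser. Its last column is headed day 30 with an allowed range of days 28 to 35. Three things are ticked there:

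- the row "Final diagnosis, duration of bacteraemia, mortality, complexity of infection", which is ticked in no other column;
- the death-only serious adverse event row, whose other ticks are on days 2 to 7;
- end of trial.

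The text after the table ties the mortality reading to closure: "At the end of the trial participation, mortality, lost-to-follow-up, time to negative SAB blood culture" and further items are then taken from the medical record. The same window appears under Sample analysis for the participant survey: "On day 30 (28–35), a proportion of the trial subjects will be asked about their experience".

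**The concern.** A record read on day 28 or 29 complies with Table 2 but cannot show whether the patient was alive on day 30. Because end of trial sits in the same column and no later look is described, nothing in the article would pick up a death on day 29 or 30 in such a patient. An analysis rule cannot repair this afterwards. It can discard deaths dated after day 30, but it cannot recover a death that happened after the record was read.

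The early side of the window also gains nothing for this item. A range of days makes sense for a questionnaire or interview that depends on reaching the patient. Mortality comes from the medical record, which can be read on any later date.

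Two outputs are exposed: the 30-day mortality figure, and the count of serious adverse events, since Ethics and dissemination states that only death counts as one.

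**Working it through.** The article gives no figure for deaths expected or missed, so there is none to reproduce. The check sizes the worst case, in which every record is read on day 28.

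**Inputs**

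- N = 95 (Hypothesis and sample size calculations).
- Background mortality: "a 30-day and 90-day mortality rate ranging from 14%–23% and 24%–32%, respectively" (Background).
- Window: days 28 to 35 (Table 2). Endpoint: day 30 (Endpoints).

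**Step 1: days at risk of being missed.** Early side: 30 − 28 = 2 days (days 29 and 30). Closure dates can differ by 35 − 28 = 7 days, but for a 30-day endpoint only the early 2 days lose information. A record read on days 30–35 contains everything needed to classify a death by its date.

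**Step 2: expected deaths by day 30.** 95 × 0.14 = 13.3 and 95 × 0.23 = 21.9.

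**Step 3: deaths on days 29–30, constant hazard over days 0–30 (assumption A).** With S(30) = 1 − m30 and S(28) = (1 − m30)^(28/30), missed deaths = 95 × [S(28) − S(30)].

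- m30 = 14%: 0.86^(28/30) = 0.8687, and 95 × (0.8687 − 0.86) = 0.8. The 14% would be read as 13.1%.
- m30 = 23%: 0.77^(28/30) = 0.7835, and 95 × (0.7835 − 0.77) = 1.3. The 23% would be read as 21.6%.

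**Step 4: deaths on days 29–30, hazard implied between day 30 and day 90 (assumption B).** With h = −ln[(1 − m90)/(1 − m30)]/60, missed deaths = 95 × (1 − m30) × [exp(2h) − 1].

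- 14% and 24%: h = 0.00206 per day; 0.34 deaths.
- 23% and 32%: h = 0.00207 per day; 0.30 deaths.
- Mixed pairings: 14% with 32% gives 0.64, and 23% with 24% gives 0.03.

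**Step 5: against sampling error.** The 95% half-width of the mortality proportion is 1.96 × √[m(1 − m)/95], which is 7.0 points at 14% and 8.5 points at 23%. The largest shortfall in Step 3 is about 1.4 points.

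**The case against.** The strongest reply is that the running text already fixes both the duration and the outcome collection at day 30, and the endpoint is named as 30-day mortality. The window would then be only a tolerance in a table heading. This has weight: deaths can be missed, but the article does not show that they will be. It does not remove the point, because the text sends the reader to Table 2, staff may well work from the schedule, and the table expressly permits days before the endpoint's own time point. This is a stated rule, not a detail left to a fuller document.

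Some stronger readings are tempting and are not supported:

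- *The reported figure would be a mixture of 28- to 35-day mortality.* Nothing says that deaths on days 31–35 would be counted as 30-day deaths, and a late record read can be cut off by date of death. Even if they were counted, the Background rates imply 95 × (0.09 to 0.10) × 5/60 = 0.7 to 0.8 deaths, pairing the low ends and the high ends. Carrying the average day 0–30 hazard forward would overstate this.
- *The figure would be compared with the published 14%–23%.* That range is introductory background, and neither Endpoints nor Statistical analysis plans such a comparison.
- *A safety conclusion would change.* Deaths are checked on days 2 to 7 and again at the final reading, and only events with a likely link to cloxacillin go to the regulator. The gap is confined to days 29–30.

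The eligibility criteria also exclude endocarditis, moribund and unconscious patients, which plausibly lowers mortality below the background range and shrinks the numbers further.

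**Conclusion.** The point holds as an inconsistency with a small effect. Table 2 permits mortality, the final death check and closure from day 28, while the endpoint and the running text require day 30, and no later check is described. Deaths on days 29–30 can be missed in patients whose record is read on day 28 or 29.

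With all 95 records read on day 28, the expected loss is about 0.3 deaths under assumption B and up to about 1.3 under assumption A. The article does not give the timing of deaths, so both hazard shapes are assumptions, and the background rates may not apply to this population. The real loss should be smaller, since not every record would be read on day 28. The item is descriptive, and the plan labels secondary results exploratory. The primary endpoints and the sample size are not affected. It is worth correcting because it is easy to avoid, not because it threatens the trial.

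**What to change.** Reconcile Table 2 with the Trial procedures text:

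- Have vital status, date of death and the death (serious adverse event) check read from the record on or after day 30, for example in a window of days 30–35, with end of trial following that reading.
- State that 30-day mortality counts deaths dated up to and including day 30.
- Keep days 28–35 for the questionnaire or interview.

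The cost is about one line in Table 2, with no extra visit, sample or staff. Recruitment is planned to a preliminary date of 31 December 2026, so the change can still apply to later participants. For anyone already closed on day 28 or 29, the record could be re-read for vital status through day 30, which stays within the stated 30-day duration.
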